#### Data collection by survey

Questionnaires will be made in www.Nettskjema.no, which is secure for storing confidential data. The research team will have access to the material, and answers will be deleted at the end of the project.

#### Plans to promote participant retention

The teachers in the study are followed up closely throughout the process, and they receive emails three to four times each month with reminders and motivating comments and always before and after testing. The first author has close contact with the teachers and delivers memory cards for the video cameras to all schools before testing and collects the memory cards immediately after the testing is finished. The first author is also available via email and phone throughout the intervention period and visits the schools when necessary and at request of the teachers. The teachers also send monthly summaries by email (anonymously) so that the first author has an overview of what and how much is being done at any given time. This helps us to intervene early if someone is lagging behind in the study or do not adhere to the protocol. If participants drop out of the study for legitimate reasons such as illness, moving, behavioral changes, or that parents want to withdraw them from the study, there is no plan for further follow-up. Data will be registered as missing data.

Regarding the participants retention (students), we have the following strategies: it is a goal that the students do the work sessions once per day. The teachers have been instructed in how to motivate the students, by using reinforce that students prefer. It is also important to involve the parents as a strategy for adherence, e.g., sending updates to the parents so they also can motivate their children to participate in the intervention.

#### Procedure

Before the start of the intervention, the researcher will ensure that all the teachers have the necessary materials, video camera with memory card, and tripod. The researcher must also ensure that all the teachers can use the video camera.

#### Data management

Data will be anonymized and stored on a restricted shared drive at the University of South-Eastern of Norway (USN) at USN Safe, to which only the research team will have access. Per the informed consent, anonymized data will be retained permanently (except in the case of withdrawal during the study) and may be released to other researchers. Identifying data (e.g., video films) will be deleted after 4 years. Data entry will be completed and checked by the research staff. Video data will be sent encrypted to the USN’s secure storage devices, accessible only by the research team. Physical data will be stored in locked cabinets within the Østfold University College and accessible only by the research team. Physical anonymized data, which describes the weekly summaries from the teachers, will be stored on a password-protected laptop computer.

#### What data will be generated

There will be data that will say something about the student’s age, gender, diagnosis, IQ, AAC aid, vocabulary and communicative competence (through results from CDI, McArthur-Bates Communicative Development Inventories), results from the assessments, and time used during the intervention. The data will also provide information about the teacher’s and student’s experiences of being part of the project (social validity).

#### How the data should be described

Each student will receive a specific number (subject ID) throughout the intervention. The list of names and numbers will be stored in a locked filing cabinet in a locked office where only the researcher has the key. The numbered data will be stored in another locked filing cabinet, i.e., separate from the list with names and numbers. All tests carried out, the registration forms, and the CDIs will be marked with the students subject ID from the randomization list.

The data that will appear on each test will list the number of correct and incorrect responses. The data that will appear on student forms from each work session will list also the correct and incorrect responses as well as the time used. It is particularly important to measure the students work progress, because they have to achieve at least 80% correct responses before they can move on to the next folder.

The data that will be collected on social validity will inform the researchers whether the students have liked working on the reading program and if they would like to continue. For children who use AAC to communicate, assessing consumer satisfaction should involve the AAC user to the greatest extent possible [52]. Directly asking the student about their experiences during and after the intervention may increase intervention relevance to the student and possibly increasing motivation to adhere to and complete the intervention [53]. In connection with data from the teachers’ survey, they will say something about the teachers’ experiences with the reading program and the reading material.

#### Randomization

The four baselines will be randomized using PASS23 via Wei’s urn algorithm that minimizes unbalanced groups. Wei’s urn randomization algorithm dynamically changes the group assignment probabilities based on the degree of imbalance to achieve longitudinal balance between groups [54].

#### Allocation concealment

To protect the assignment sequence until the allocation of when the baseline will start, a “third-party” assignment will be used. A biostatistician will be called every time a student has all the inclusion and exclusion criteria filled, and he will also be responsible for generating the random generation. The enrollment of the student will be done by the first author of this manuscript ([name]).

#### Blinding

This is an open-label trial because it is impossible to mask the students when the intervention starts (baseline). Moreover, given that the first author of this manuscript is the research leader of the project, she will coordinate the field work and will act as one of the assessors based on her training on the assessment of the outcomes and intervention and thus will not be able to remain blinded from the study subjects. Since all the 18 assessments across time will be filmed after the agreement and reliability were checked by two assessors, the teachers will not be blinded on which phase of the intervention the students are assigned. However, the two assessors will code the outcomes independently to establish interobserver agreement on the coded observations.

#### Statistical analysis plans

Generalized estimating equation (GEE) with work matrix of first-order autoregressive factor will be used to the effects of the implementation of the intervention after the baseline assessment. Missing data will be treated as missing at a random mechanism via restricted maximum likelihood. The adopted significance level is 0.0125 (due to the four correlated outcomes, reducing the false discovery rates). For interobserver quality check, we will calculate the interobserver agreement using intraclass correlation (ICC) [55]. There are no plans to conduct additional analyses (e.g., subgroups or adjusted analyses).

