### Design

This study will be conducted with multiple single-case design with four multiple randomized baselines, where the shortest baseline has two assessments and the largest has five, and the intervention phase has 18 assessments across time. We have recruited 40 students with intellectual disabilities who require AAC.

To evaluate the effectiveness of the intervention effects in this study, the What Works Clearinghouse (WWC) single-case design technical documentation provides appropriate study analysis techniques [20]. Andzik and Chung [8] recommend that researchers follow these quality guidelines for single-case experimental studies to ensure internal validity of the study with reliable measures (Fig. 1).

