### Sample size calculation and power

The power calculation is based on Hedges et al. [31] where the input parameters are as follows:Number the phases is equal to one (i.e., we have one baseline phase and one intervention phase)Intraclass coefficient correlation of 0.5Autoregressive effect 0.5Alpha error probability of 0.016 (giving we have three primary outcomes)Minimum number of observations per phase is threeMinimum detectable effect size is a Cohen’s *d* of 0.5

Under those input parameters, our power is 75.84%; however, it is important to note that our study has an unbalanced design (different amounts of observations per phase resulting in the intervention phase being larger than the baseline). This is designed specifically to improve the adherence of the students and their families on the study. In our experience, being without intervention for more than 6 months (e.g., baseline phase) would reduce the interest and adherence of the participants in the trial. Therefore, our observable power will be superior than the above reported. The estimation of the power was conducted using the Power Analysis and Sample Size software (PASS) [32].

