#### Assessment of the outcomes

A registration form has been developed to use during the assessment and data collection of outcomes. The form is designed so the teacher can click whether the student answers options 1, 2, 3, or 4. It is the student’s teacher who will carry out all the tests. The teacher must register correct or incorrect responses during the assessment. Only the teacher and the student will be present during the testing, and all test situations will be filmed. Each student will receive an individual follow-up plan that will describe in detail when tests will be carried out and when the intervention will start. Within each phase, 20% of the recorded films will be randomly selected and evaluated by two external raters at item-level across the five primary outcomes. Agreement between the two raters and the teachers will be checked, and in case of agreements below 80%, all the films will be checked.

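### The flat 0.0125 level is a valid family-wise rule mislabelled as false-discovery control; Holm's step-down test at the same family size would recover some power at almost no cost

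*Protocol article*

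**What the plan says.** The Statistical analysis plans section fixes one level for every test: "The adopted significance level is 0.0125 (due to the four correlated outcomes, reducing the false discovery rates". It describes no step-down or false-discovery procedure, and it gives no value for the correlation between outcomes.

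The Sample size calculation and power section works at a different level, 0.016, tied to three primary outcomes. It assumes d = 0.5, an intraclass correlation of 0.5, an autoregressive effect of 0.5 and at least three observations per phase, and it reports: "Under those input parameters, our power is 75.84" (per cent). It adds that the achieved power should be higher, because the intervention phase has more observations than the baseline.

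The number of outcomes varies across the article. The Primary outcomes section lists three and the Secondary outcomes section two more. The significance level is set for four. The Assessment of the outcomes section has films "evaluated by two external raters at item-level across the five primary outcomes", and the Video coding section repeats that count.

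The sample is fixed: "We have recruited 40 students with intellectual disabilities who require AAC".

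**The concern.** There are two issues. First, the sentence gives false discovery as the purpose of a rule that controls something else. Dividing 0.05 by the number of outcomes and testing each at the quotient bounds the chance of any false positive. A reader cannot tell which error rate the trial means to control.

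Second, the single-step cut ignores the results of the other outcomes. One programme trains all the skills together, so several outcomes improving at once is what the trial hopes to see, and that is where a single-step rule loses most to a step-down rule. With three primary outcomes and p = 0.004, 0.020 and 0.030, flat 0.05/3 = 0.0167 gives one positive finding. Holm compares them with 0.0167, 0.025 and 0.05 and gives three, at the same 5% family-wise bound. Recruitment is complete, so the testing rule is one of the few remaining ways to gain power.

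**Working it through.** **The level.** 0.05/4 = 0.0125 exactly, so the rule is Bonferroni for four outcomes. With four independent tests the family-wise error is 1 − (1 − 0.0125)^4 = 0.049. The level in the power section is 0.05/3 = 0.0167, truncated to 0.016.

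**The stated power.** I tried to reproduce 75.84% from a within-student phase contrast with the listed inputs, 40 students and three observations per phase. With d scaled by the total SD this gives 98.5 to 99.1% (two-sided). With d on the within-student SD it gives 79.7 to 83.1%, and with unpaired phase means 51.4 to 53.3%. None matches. The article does not give the exact procedure or list the number of cases among the inputs, so this does not show that 75.84% is wrong. I take the figure as stated and show what happens if it is too low.

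**Implied effect.** Two-sided tests are assumed, since the article does not say. Non-centrality = z(1 − 0.016/2) + z(0.7584) = 2.409 + 0.701 = 3.110. Power at level α is then Φ(3.110 − z(1 − α/2)):

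- α = 0.0125: Φ(3.110 − 2.498) = 73.0%
- α = 0.05/3: Φ(3.110 − 2.394) = 76.3%
- α = 0.05: Φ(3.110 − 1.960) = 87.5%, the ceiling for Holm

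**Holm against Bonferroni at the same family size.** Simulation with 400,000 draws of equicorrelated normal statistics, equal effects where an effect exists, and 5% family-wise error. The correlation r is an assumption. Entries are power per truly improved outcome.

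| Family | Truly improved | Flat | Holm, r = 0 / 0.5 / 0.8 | Gain in points |
|---|---|---|---|---|
| 3 | 3 | 76.3% | 84.9 / 83.3 / 82.0% | 8.6 / 6.9 / 5.7 |
| 3 | 2 | 76.3% | 79.9 / 79.3 / 78.7% | 3.6 / 3.0 / 2.5 |
| 3 | 1 | 76.3% | 76.6 / 76.4 / 76.4% | about 0.1 or less |
| 4 | 4 | 73.0% | 83.6 / 81.5 / 79.9% | 10.6 / 8.5 / 6.9 |
| 4 | 3 | 73.0% | 78.9 / 77.8 / 77.1% | 5.8 / 4.8 / 4.1 |
| 4 | 2 | 73.0% | 75.5 / 75.2 / 74.8% | 2.6 / 2.1 / 1.8 |
| 4 | 1 | 73.0% | 73.1 / 73.1 / 73.0% | about 0.1 or less |

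With three outcomes all improved and r = 0.5, the chance that all three are significant rises from 56% to 72%.

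**Error rate.** When no outcome improves, the two rules have the same family-wise error at the same family size: 0.049 at r = 0, about 0.044 (three outcomes) or 0.043 (four) at r = 0.5, and 0.035 or 0.032 at r = 0.8.

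**If true power is higher.** With 95% power at 0.016 and every outcome improved, the gain falls to about 2 to 3 points for three outcomes and 3 to 4 for four. At 98% it is about 1 to 2 points.

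**The case against.** The strongest reply is that flat Bonferroni is a valid, conventional and conservative choice, with confidence intervals that match its decisions, and that preferring Holm is a matter of taste. The first part stands: nothing is wrong with the error control, and this is not the correction of an invalid test. The second part is weaker, because Holm at the same family size never rejects less, needs no added assumption and costs one sentence.

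It is also fair that the gain depends on circumstances. It needs several outcomes to improve together, it shrinks as power rises, and the article itself expects power above 75.84%. Those limits stand.

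Three stronger readings are tempting, and the documents do not support them.

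- A reader might compare flat 0.0125 with Holm on three outcomes and infer a gain of up to 12 points at equal family-wise error. That mixes two changes. About 3.3 points (76.3% − 73.0%) come from shrinking the family from four to three. Flat 0.0125 on three outcomes also has a family-wise error of only 0.027 to 0.037, so the two rules do not spend the same error.
- A reader might infer that Holm exploits the correlation the plan mentions. It does not, and its gain falls as correlation rises.
- A reader might infer that Holm delivers the false-discovery control the sentence names. It is also a family-wise method. A Benjamini-Hochberg test would match the present wording, but it gives up strong family-wise control.

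**Conclusion.** The point holds as a wording correction and an efficiency improvement. A flat 0.05/4 cut is described by an error rate it does not target, and a uniformly more powerful rule with the same guarantee is available.

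The size rests on the stated 75.84% at 0.016, two-sided tests, equal effects and correlations from 0 to 0.8. On those assumptions the like-for-like gain per outcome is about 6 to 9 points (three outcomes) or 7 to 11 (four) if all improve, about 2 to 6 if all but one or two do, and essentially zero if only one does. It drops to a few points or less if power is really 95% or more. The conflicting counts of three, four and five outcomes must be reconciled before any multiplicity rule can be applied, Holm included.

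**What to change.** First reconcile the number of primary outcomes across the power section, the Primary outcomes section, the Statistical analysis plans section and the two passages on video rating. Then, in the Statistical analysis plans section, replace the flat 0.0125 with Holm's procedure at two-sided 5% family-wise error across the primary outcomes. If the family is the three listed under Primary outcomes, compare the smallest p-value with 0.05/3, the next with 0.05/2 and the largest with 0.05, stopping at the first failure. Sight words and decoding would then be reported outside this family and labelled secondary, as the article already lists them. Replace the reference to false discovery rates with a statement that the family-wise error rate is controlled at 5%.

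The cost is about one sentence and no extra data, to be settled before outcome data are analysed. The drawback is that confidence intervals matching Holm decisions are less simple, so unadjusted or Bonferroni intervals would be reported beside them and labelled as such.

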#### Primary outcomes

Primary outcomes will be assessed 18 times in equidistant time points, every month, across 18 months. All the below described tests were developed by the first and second author. To the best of our knowledge, there are no such available tools in Norwegian to assess this population who uses AAC with demonstrated evidence of validity. They are centered on the following phonological awareness skills domains:Sound blending [score ranging from 0 to 10] measured by adapted tests in line with the reading material “Lesing for alle.” Researcher-designed test. Testing in sound blending involves testing the student’s ability to combine individual sounds into words. The students will see a sheet of paper with four symbols. In the instructions, the target word will be presented by expanding the individual sound in the word. For example, “sss-uuu-nnn.” The students have to listen to the sounds, put the sounds together in their head, and then point to the symbol that belongs to the word. This test consists of 10 tasks. The teacher will make no comments on the accuracy of student’s selections but just comment “good work” for the motivation.

Example of one test task in sound blending:

Wigdit symbols [47].2)Letter-sound correspondence [score ranging from 0 to 25] measured by adapted tests in line with the reading material “Lesing for alle.” Researcher-designed test. Testing in letter-sound correspondence involves testing the student’s ability on the correspondence between the sounds of speech (phonemes) and the written letters that represent speech (graphemes). The instructor asks the student to choose, for example, the letter sound “*a*.” The student must then discriminate between the target sound and three others. This test consists of 25 tasks.3)Phoneme segmentation [score ranging from 0 to 10] measured by test in line with the reading material “Lesing for alle.” Researcher-designed test. Testing in phoneme segmentation tests the student’s ability to segment the first phoneme of the word (e.g., *s* for *sun*). Then, the student must select the symbol for the word that begins with the target phoneme. The student must discriminate between four symbols. The instruction asks the student to find the word that starts with, for example “*a*.” This test consists of 10 tasks.

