#### Secondary outcomes

The time frame is as follows: two time points during baseline phase, two during intervention (months 1, 12, and 18). In the same way as described above, we have a lack of evidence in terms of validity in the following tests in Norwegian, and those assessments were specially developed for this population. Part of this study is focused on providing evidence based on other variables [50].Recognition of sight words [score ranging from 0 to 10] measured by adapted tests in line with the reading material “Lesing for alle.” Testing in sight words measures the student’s ability to recognize words learned by sight, i.e., words that are difficult to decode. The student must discriminate between one target sight word and three others. The three other words consists both of other novel sight words, words that start with the same first sound as the target word and words of similar form. This test consists of 10 tasks with consonant–vowel-consonant (CVC), CV, VCVC, CCVC, VCCVC, and VCC words.Decoding [score ranging from 0 to 20] measured by adapted tests in line with the reading material “Lesing for alle.” Testing in decoding tests the student’s ability to (1) recognize the letters in the word, (2) associate each letter with its corresponding sound, (3) hold these sounds in sequence in working memory, (4) blend the sounds to determine the word, (5) retrieve the meaning of the word [51], and, finally, (5) select the symbol that represents the word. The students must discriminate between four symbols, where one symbol represents the target word, and the other three consist of words with the same first sound, novel words, and words with similar forms. This test consists of 20 tasks with both CVC, VCC, and CCV words, for example, *bil* (car), *ost* (cheese), and *tre* (tree). Ten words will be familiar from the reading material, and 10 words will be novel; the words are thus not being worked explicitly through the reading intervention.

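### The test level of 0.0125 rests on a count of four outcomes that the protocol never lists, and it differs from the 0.016 behind the stated power, which does fit the three listed primary outcomes

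*Protocol article*

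**What the plan says.** All places are in the protocol article.

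- **Primary outcomes** lists three tests, given monthly: "Sound blending [score ranging from 0 to 10] measured by adapted tests", "Letter-sound correspondence [score ranging from 0 to 25] measured by adapted tests" and "Phoneme segmentation [score ranging from 0 to 10] measured by test in line with the reading material".
- **Secondary outcomes** lists two, given at a few time points only: "Recognition of sight words [score ranging from 0 to 10] measured by adapted tests" and "Decoding [score ranging from 0 to 20] measured by adapted tests".
- **Sample size calculation and power** sets alpha at 0.016 on the ground that there are three primary outcomes, and reports: "Under those input parameters, our power is 75.84" (per cent).
- **Statistical analysis plans** sets a different level: "The adopted significance level is 0.0125 (due to the four correlated outcomes, reducing the false discovery rates".
- **Assessment of the outcomes** says that a sample of the films will be "evaluated by two external raters at item-level across the five primary outcomes". **Video coding** repeats this.

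**The concern.** The threshold for declaring an effect and the set of outcomes it covers should each have one value before analysis. Here the power section and the analysis section give different thresholds, and the analysis section justifies its own by a count that matches neither outcome list nor their total. A p-value between 0.0125 and 0.016 on sound blending, for example, would succeed at the level used for power and fail at the level adopted for testing.

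The family is also blurred because the video-rating text calls five outcomes primary. In an open-label trial whose tests are given by the student's own teacher, it should be settled in advance whether sight words and decoding can support a confirmatory claim.

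**Working it through.** **1. Which count does each level fit?** With an overall 5% split equally over k outcomes, the per-test level is 0.05/k.

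| k | 0.05/k | Defined in the article? |
|---|---|---|
| 3 | 0.01667 | Yes: the listed primaries. Cut to three decimals this is 0.016 |
| 4 | 0.0125 | No list of four |
| 5 | 0.01 | Three primary plus two secondary; 0.01 is used nowhere |

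So 0.016 fits the three primaries (3 x 0.016 = 0.048). The level 0.0125 is exactly 0.05/4 and fits no listed set.

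**2. Family-wise error at 0.0125.**
- Three outcomes: bound 3 x 0.0125 = 0.0375; if independent, 1 - 0.9875^3 = 0.037.
- Five outcomes: bound 5 x 0.0125 = 0.0625; if independent, 1 - 0.9875^5 = 0.061.

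**3. Can the 75.84% be reproduced?** The inputs given are d = 0.5, intraclass correlation 0.5, autocorrelation 0.5, three observations per phase and alpha 0.016. The number of cases and the sidedness are not among them. I tried a contrast of phase means within cases:
- Variance factor under first-order autocorrelation: (2 x 5.5 - 2 x 1.53125)/9 = 0.882.
- Non-centrality = 0.5 / sqrt(0.882 x (1 - 0.5)/m) for m cases.
- m = 40: non-centrality 4.76; two-sided power 98.5% (t, 39 df) to 99.1% (normal).
- m = 20: non-centrality 3.37; power 75.7% (t, 19 df).
- m = 40 with between-case variance added to the contrast, which is not standard: 76.7% (t, 39 df).

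The near matches need assumptions that the article does not state. The figure is neither confirmed nor refuted, so I take it as given below.

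**4. Power at other levels, holding 75.84% at 0.016.** Two-sided normal approximation:
- Implied non-centrality = z(0.992) + z(0.7584) = 2.409 + 0.701 = 3.110.
- At 0.05/3: Phi(3.110 - 2.394) = 76.3%.
- At 0.0125: Phi(3.110 - 2.498) = 73.0%.
- At 0.01: Phi(3.110 - 2.576) = 70.3%.

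Range at 0.0125 under other assumptions: 72.4% (t, 19 df), 72.7% (t, 39 df), and 72.7% if one-sided (2.144 + 0.701 = 2.846; Phi(2.846 - 2.241)). At 0.05/3 the same variants stay within 76.3% to 76.4%.

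**The case against.** Much can be said for the plan.

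- **The primaries are clear where outcomes are defined.** There are three, with a monthly schedule that sets them apart from the two secondaries, and 0.016 agrees with them. A reader might infer that neither level fits the listed outcomes. That is wrong for 0.016.
- **Four is never called a number of primary outcomes.** The analysis section speaks only of correlated outcomes. It still corresponds to nothing the article lists.
- **Five appears only in the text on rating films.** It equals three plus two, and the second occurrence repeats the first, so the word primary there is most plausibly a slip. A reader might infer that the type I error exceeds 5%. The article does not support this for the listed primaries, where 0.0125 is stricter than needed. The 6.25% bound requires all five to be confirmatory at that level.
- **The article expects real power above the stated figure**, because the intervention phase is longer than the baseline. That may be so, and the gap between the two levels would then shrink: in the 40-case t calculation above it is 98.5% against 98.1%. It does not make 75.84% the power of a test at 0.0125.
- **The reference to false discovery rates is a matter of terms.** An equal split is built to control family-wise error. With the right count it also bounds the false discovery rate, so the aim is not defeated.

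These points reduce the size of the problem. They do not reconcile the two thresholds.

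**Conclusion.** The contradiction stands as written. The adopted level of 0.0125 belongs to no outcome set in the article and differs from the level on which the stated power rests. For the three listed primaries the consequence is a needlessly strict test (3.75% of 5% spent) and about 3 points less power than stated: roughly 73% instead of 75.84%, with a range of 72.4% to 73.0% over the approximations tried. The power figures depend on accepting 75.84%, which could not be checked from the listed inputs. An error bound above 5% arises only on the reading that all five outcomes are confirmatory.

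The point is modest in size, but it concerns the rule for declaring success and should be settled before analysis.

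**What to change.** 1. State that the confirmatory family consists of the three outcomes listed under Primary outcomes.
2. Use one per-test level in both the power and the analysis sections. Either take 0.05/3 (about 0.0167) and give power as about 76%, or keep 0.0125, say that it is deliberately stricter than three outcomes require, and restate power as about 73%. It is better to rerun the power software at the chosen level than to rely on the approximation here.
3. Under Assessment of the outcomes and Video coding, replace the count of five primaries by three primary and two secondary outcomes.
4. Say that sight words and decoding are reported outside the confirmatory family.
5. Replace the reference to false discovery rates by family-wise error, and drop the count of four.

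The cost is wording in four sections and one rerun of the power calculation, with no extra data. As an option, Holm's procedure over the three primaries at a family-wise 0.05 would gain power without further data. That is an improvement, not a correction of the error described here.
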